## Methods/design (process evaluation)

The trial will be subjected to a rigorous qualitative process evaluation. Process evaluations within trials explore the: (1) implementation; (2) receipt; and (3) setting of an intervention and help in the interpretation of the outcome of results
[40]. This can help improve the validity of the intervention findings alongside helping to explain specific reasons why an intervention succeeded or failed
[41]. A process evaluation answers the question ‘where does the intervention work, how and why?’. A key component of a process evaluation is that of implementation ‘fidelity’ which measures the degree to which an intervention was implemented as intended
[42].

The methods used to conduct a process evaluation of the trial will be:

detailed fieldworker diariesin-depth ethnographic observation of the APMstelephone interviews with APM leadbrief questionnaire to all staffcollection of key information from intervention wards

The timescales for these process evaluation methods have been mapped onto the main trial timescales and detailed in Additional file
1: Appendix 6.Researchers will keep qualitative fieldwork diaries during the life of the trial to record their daily thoughts about what is occurring ‘on the ground’. Fieldwork diaries are informed by their regularity and personal and contemporaneous nature [43]. It is expected that researchers will write entries several times a week. The content of the diaries will focus on the culture or dynamics of a ward that may hinder or support intervention implementation alongside the fieldworker’s own personal reflection on events that have taken place [43]. Researchers will meet regularly to ensure that momentum is maintained with diary writing and to review the content to examine similarities and differences in research experiences on certain wards. Findings from these diaries will help inform how the trial has been implemented and received by the wards. In the pilot study, we are already implicitly aware of how different cultures on different wards may have influenced how the intervention was implemented and how much of this can be identified by the fieldworkers on site. Recording of this tacit knowledge will improve the validity of the intervention findings.One of the most important processes to occur within this trial is that of the action planning meeting (APM) where members of staff on individual wards meet to actively consider their feedback reports based on the safety data generated from patients responses. Correspondingly, APMs form the most ‘active ingredients’ of this trial as the teams digest the information from the feedback reports and consider which action plans to make. It is therefore vital that in depth ethnographic observation of these meetings forms a core part of the process evaluation if the research team are to understand how the intervention works. A research team using an intervention to improve lung cancer outcomes [42] found that observation of MDT meetings was a core element of their evaluation. The APM will be digitally recorded to allow the researchers to ‘revisit’ the meeting at a later date. Researchers will make detailed field notes straight after the APM has finished. They will start by making descriptive observations to describe ‘what, who, where and how’ [43] and then focus on processes occurring during the APM. Processes may include meanings, spaces, participation, relationships and settings [44]. A highly detailed account will be maintained. The last stage will be the researcher’s own interpretations of the observational period paying attention to the minutiae of how the ward staff have received the intervention, how they relate to each other as a team regarding the trial and how they plan action points.Short, structured telephone interviews will be undertaken with the nominated PRASE lead for each intervention ward involved in the APM. Participants will be asked to rate the implementation of their action plans by attributing Yes, Partial or No to each action plan. Interviewers will then probe for context as to why action plans were only partially or not implemented alongside ascertaining how successful action planning was achieved. Additional open ended questioning will primarily focus on how engaged and satisfied APM members were with the intervention. Interviews will be undertaken at 6 months and 12 months into the trial.At the 12-month stage, a brief questionnaire will be dovetailed into the staff safety culture survey. We will include four items to measure the ‘reach’ of the intervention, that is, how far the knowledge of the intervention has spread among staff on the ward who are not involved in the action planning groupThe collection of key information from intervention wards is an important part of this process evaluation. The research team will monitor the following:Did the ward staff attend an action planning meeting which was facilitated by a researcher from the PRASE team?How many times a ward postponed or cancelled an APM, if any?Were action plans made by the ward?Is there any documented evidence of this?Did the ward take part in a telephone interview about the study?Attendance at whole-Trust meetings (start-up, mid-point, closing)

### Process evaluation analysis

Fieldworker diaries **-** these will be read and interrogated for common themes arising from the notes that differing researchers have made. The diaries kept during the first data collection period will be used to formulate a more prescriptive template for diary recording in the second and third data collection periods. It is likely that information will emerge about the hospital Trusts in general and then more specifically about individual wards. At this point in time, it is unknown what fieldworkers will write about and therefore diary writing during the phase one data collection period is a pilot activity in itself in order to produce a diary template for the second and third data collection periods. However, all data arising from this period will be treated as real data and included in the final analysis. We expect diary data to be subject to a thematic analysis, using a framework analysis structure [45].In depth ethnographic observation of APMs - An examination of the digital tape recording of the APM will focus on core themes related to action planning. These may include an examination of:The rationale behind the action plans which the group chose to makeWhether ward staff chose to make systemic, upstream plans or chose ‘quick fixes’ and the context behind thisPotential action plans which were discussed but not acted upon and the reasons why (including financial, logistic, cultural or other constraints)

These explicit data regarding what the APT discussed will be synthesised with the implicit data gathered from the facilitator’s field notes. This will give a comprehensive qualitative account of each APM. Both data sources will be synthesized and analysed, using techniques derived from adaptive theory
[46]. We anticipate that this analysis may provide explanatory power for the PMOS scores alongside an understanding of wider, contextual organisational issues at play.c)Structured interviews - An *a priori* coding framework will be devised, structured around key categorisations for why action plans were successful, partially successful or failed to be implemented. This could include concepts of autonomy, ownership or resource. However, the coding framework will also give flexibility to data that arise from the participants themselves. Similarities and differences will be interrogated between wards - particularly in the same Trust - to understand how similar action plans were implemented on some wards but not on others and the rationales behind this. Findings related to engagement and satisfaction with the intervention will point the research team towards which elements of the study ward staff may have struggled with and which elements they embraced.d)Questionnaire to all staff - Mean scores on four Likert questionnaire items will provide an indication of the extent to which ward staff have been exposed to the different aspects of the intervention, for example, the data collection, feedback, action planning and implementation of actions. A summed score across these four items will be used as a measure of ‘reach’ in the main trial analysis.e)Collection of key information from intervention wards - The recording of key factual information listed above will enable ‘scores’ to be derived regarding the basic fidelity of the intervention implementation for each ward (see next section for further details).

### Assessment of fidelity

An assessment of fidelity is an important component of the evaluation of complex interventions, sometimes described as the ‘black box’ of interventions
[47]. Following Hasson *et al.*
[41, 48] and Carroll *et al.*
[49], we propose a systematic assessment of implementation fidelity of the PRASE intervention. The framework for this assessment is outlined in Additional file
1: Appendix 7, and is an adapted version of the Conceptual Framework for Implementation Fidelity
[49], which has recently been used successfully in a health service intervention
[48]. Three of the authors ([name]) agreed the key components of the intervention, and then which components were appropriate for the fidelity assessment. Some components were not deemed appropriate for a fidelity assessment as this aspect of the intervention is under the direct control of the research team (for example, ‘collection of feedback from patients about safety incidents and positive experiences of care’; see Additional file
1: Appendix 7 for other examples).

Adherence will be assessed for each intervention component, which are:

Attendance and contribution to pan-Trust Start Up MeetingHolding a multi-disciplinary Action Planning Meeting to consider patient feedback about safety and quality (x 2 per intervention ward)Creation of action plans in response to patient feedbackImplementation of action plansAttendance and contribution to pan-Trust Mid-Point MeetingAttendance and contribution to pan-Trust Closing Meeting

Other components of the intervention exist but these are not subject to fidelity adherence as they are researcher controlled (see Additional file
1: Appendix 7)

We will use the following criteria to assess each of the above listed intervention components:

Content - was the intervention component implemented as planned?Reach - what proportion of the target group participated in this intervention component?

Following Hasson *et al.*
[41, 48] and Carroll *et al.*
[49], the authors also agreed which of the potential moderating factors may impact on the adherence of participating wards in each of the fidelity components. Only three potential moderating factors were selected, as the others were deemed to be under the control of the researchers within the study. The three selected were:

Context (including management support) - what factors at political, economic, organizational and work group levels affected the implementation?Responsiveness - how were the participants engaged with the intervention component? How satisfied were the participants with the intervention component? How did the participants perceive the outcomes and relevance of the intervention component?Quality of delivery - how was the quality of delivering the intervention components?

These moderating factors will be assessed using data from the process evaluation, utilising whichever method(s) give the most accurate data to answer the relevant moderating factor question. For instance, it is anticipated that the first question under ‘responsiveness’ will be assessed via the observation of the APMs and facilitators’ notes while the second and third questions will be assessed from data gathered in the structured telephone interview stage.

Adherence to the different intervention components will be ‘scored’ on a categorical scale ranging from 0 to 3, with 0 representing ’no adherence’, 1 representing ‘some adherence’, 2 representing ‘mostly adhering’, and 3 representing ‘full adherence’. The assessment of adherence will be undertaken using the full range of information following completion of the process evaluation and largely based on satisfaction in relation to each of the moderating factors. Each intervention component will be independently scored by three members of the research team, before agreement on the final score for each ward reached through discussion and consensus. The final score will be available to be used as a covariate in the final quantitative analysis, although it is anticipated that results will be presented with and without the fidelity score.

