**Methods/design:**

A multi-centre, cluster, wait list design, randomised controlled trial with an embedded qualitative process evaluation. The aim is to assess the efficacy of the PRASE intervention, in achieving patient safety improvements over a 12-month period.

The trial will take place across 32 hospital wards in three NHS Hospital Trusts in the North of England. The PRASE intervention comprises two tools: (1) a 44-item questionnaire which asks patients about safety concerns and issues; and (2) a proforma for patients to report (a) any specific patient safety incidents they have been involved in or witnessed and (b) any positive experiences. These two tools then provide data which are fed back to wards in a structured feedback report. Using this report, ward staff are asked to hold action planning meetings (APMs) in order to action plan, then implement their plans in line with the issues raised by patients in order to improve patient safety and the patient experience.

The trial will be subjected to a rigorous qualitative process evaluation which will enable interpretation of the trial results. Methods: fieldworker diaries, ethnographic observation of APMs, structured interviews with APM lead and collection of key data about intervention wards. Intervention fidelity will be assessed primarily by adherence to the intervention via scoring based on an adapted framework.

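### The 0–3 adherence grade is to rest largely on the moderating factors, although the plan sets Content and Reach as the criteria for adherence and treats moderators as influences on it

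*Protocol article*

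**What the plan says.** The protocol article describes fidelity in four places.

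- The abstract (Methods/design) states: "Intervention fidelity will be assessed primarily by adherence to the intervention via scoring based on an adapted framework".
- The opening of Methods/design (process evaluation) says that fidelity "measures the degree to which an intervention was implemented as intended".
- Process evaluation analysis, item (e), says that the factual information recorded for intervention wards will allow scores "to be derived regarding the basic fidelity of the intervention implementation for each ward", and points to the next section for detail.
- Assessment of fidelity, the section so referred to, lists six components and continues: "We will use the following criteria to assess each of the above listed intervention components". Two criteria follow. The first is "Content - was the intervention component implemented as planned"; the second, Reach, asks what share of the target group took part.

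Assessment of fidelity then turns to a different set of items. It reports that "the authors also agreed which of the potential moderating factors may impact on the adherence of participating wards", and names three: Context, Responsiveness and Quality of delivery. Participant satisfaction is one of the questions under Responsiveness.

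The scoring rule closes the section. Each component is graded from 0 (none) to 3 (full) for adherence, "using the full range of information following completion of the process evaluation", and the grade is "largely based on satisfaction in relation to each of the moderating factors". Three team members score independently and then agree a final score by consensus. That score may be used as a covariate in the quantitative analysis, with results expected both with and without it.

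**The concern.** The scoring rule rests mainly on items that the same section has just presented as possible causes of good or poor adherence, and it does not name the two criteria that the section set for adherence. Two things are at stake.

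The first is what the score measures. The process evaluation is meant to help explain why the intervention succeeded or failed. For that, readers need to know whether wards did what was asked of them. A grade driven by management support, engagement or satisfaction answers a different question.

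The second is what can be learned about the moderators. If Context, Responsiveness and Quality of delivery largely determine the adherence grade, an association between them and that grade is built in. It says nothing about whether they influenced delivery, which is the role the plan gives them.

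**Working it through.** The plan gives no figure on this point and no arithmetic applies. The check is to set the statements side by side.

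1. **What is to be measured.** Methods/design (process evaluation): the degree of implementation as intended. The abstract agrees that this is done mainly by scoring adherence.
2. **What it is to be measured with.** Assessment of fidelity: Content and Reach, for each of six components (start-up meeting, action planning meetings, creation of action plans, implementation of action plans, mid-point meeting, closing meeting). Process evaluation analysis, item (e), is consistent with this, since it derives basic fidelity scores from recorded facts. Those facts include whether a facilitated action planning meeting was attended, whether plans were made and documented, and whether Trust-wide meetings were attended.
3. **What the moderators are.** Assessment of fidelity: factors that may act on adherence. They are listed after the criteria and apart from them.
4. **What the scorers are told to do.** Assessment of fidelity, scoring rule: grade adherence largely on satisfaction in relation to the moderators.

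Statements 1 to 3 agree with each other. Statement 4 does not agree with 2 or 3, and so the score it produces does not match 1.

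The conflict does not depend on how one word is read. If satisfaction means participants' contentment, the grade rests on one question under one moderator, extended to the others. If it means that a moderator's conditions were fulfilled, the grade still rests on the moderators.

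Two cases show the effect of following the rule literally:

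- A ward holds both action planning meetings and implements all its plans, but has little management support and dissatisfied staff. On Content it is fully adherent. Under the scoring rule it could be graded low.
- An enthusiastic, well-supported ward implements little. On Content it adheres poorly. Under the scoring rule it could be graded higher than its delivery warrants.

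Both are possibilities under the text, not predictions of how the team would score.

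**The case against.** The strongest reply is that this is one loosely worded sentence. The same sentence draws on all the information from the process evaluation, which includes the factual records. The grades are labelled by degree of adherence, not of satisfaction. Implementation of action plans is a component of its own, and each plan is rated Yes, Partial or No in the telephone interviews, so a ward that implemented little would be hard to grade as fully adherent. Three independent scorings followed by consensus give some protection. The framework is in Additional file 1, Appendix 7, which is not shown here and may say more.

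Much of this stands, and it limits the point. Content and Reach may well contribute, so a reader should not infer that the score would carry no information about delivery. It does not remove the conflict, because the word 'largely' makes those criteria secondary. This is also not a complaint about missing detail: the article states a rule that disagrees with its own criteria, and an appendix would not delete that sentence.

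Three stronger inferences are tempting and are not supported:

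- **A numerical swing.** One could add the grades over six components and show how far a fully delivering ward might fall. Nothing in the article says that the grades are summed, and any assumed fall would be the reader's choice.
- **Contamination by trial results.** One Responsiveness question asks how participants perceive outcomes, but it means the outcomes of the intervention component. The primary outcomes are patient-completed questionnaire scores and routine Safety Thermometer data. A link between the two is conjecture.
- **Unmasked scoring.** The article does not say whether scorers will have seen the 12-month results. A condensed article may leave that to the full protocol, and silence is not evidence that they will.

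**Conclusion.** The contradiction is real and lies within a single section. As written, the rule mixes influences on adherence into the adherence grade, so the grade would not measure fidelity as the plan defines it and could not be used to study whether the moderators affected adherence.

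The consequence is limited. It touches the process evaluation and a covariate analysis that is optional and expected to be shown with and without the score. The primary analyses described under Trial analysis do not use the score, so a reader should not infer that the comparison of the arms is at risk. The delivery records also remain available whatever the composite grade says. No magnitude can be calculated.

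The conclusion assumes that scorers would follow the sentence as printed and that Appendix 7 does not override it. It is worth correcting because the score may enter the quantitative analysis and the correction is cheap.

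**What to change.** In Assessment of fidelity, replace the scoring sentence so that each component's 0–3 grade is set from Content and Reach. The sources are already planned: attendance at Trust-wide meetings, action planning meetings held, action plans made and documented, and the Yes/Partial/No implementation ratings. Report Context, Responsiveness and Quality of delivery separately for each ward, as factors that may explain the grade. If Appendix 7 carries the same scoring rule, amend it to match.

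The cost is mainly wording. One practical point needs attention: the list of key information for intervention wards does not expressly include the share of the target group taking part in each component. The team should confirm that attendance notes and meeting observations will supply it. The downside is a less nuanced single score, offset by showing the moderators beside it.

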Action Planning Meetings (APMs) will be facilitated by a senior researcher from the Quality & Safety research team. The piloting of the PRASE intervention showed that facilitation of APMs was important for generation of concrete action plans as an outcome of the action planning meeting.

Control wards will receive no intervention during the study duration. At the end of the study, control wards will receive all their feedback reports for the three time points of data collection amalgamated into one report.

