Secondary outcomes will be analysed using similar models to the primary outcomes. Ward level covariates will be added to the primary model in order to explore their influence. Continuous measures will be compared between groups using multi-level regression modelling accounting for trust/ward where required and the minimisation factors. Categorical measures will be compared between groups using logistic regression (or ordinal logistic regression for ordinal measures) adjusting for the Trust/ward where required and minimisation factors. The validity and reliability of the PMOS and domain scores will be investigated in this population using Cronbach’s alpha and known-group comparisons. All primary and secondary outcome measures will be summarised at each time point and by intervention group using summary tables or graphs/bar charts depending on the type of data.

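### The fidelity score, and reach if used as a covariate, should be kept out of every between-arm model: the randomised effect cannot be read from a model that contains them

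*Protocol article*

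**What the plan says.** Four parts of the protocol article bear on this.

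- **Assessment of fidelity.** Each intervention component is scored "on a categorical scale ranging from 0 to 3", and a final score is agreed for each ward. On timing: "The assessment of adherence will be undertaken using the full range of information following completion of the process evaluation". On use: "The final score will be available to be used as a covariate in the final quantitative analysis". The same sentence goes on to expect that both versions, one including the score and one leaving it out, will be reported. The components are the start-up, mid-point and closing meetings, two action planning meetings per intervention ward, the making of action plans, and their implementation.
- **Process evaluation analysis.** Four Likert items are added to the 12-month staff survey. On their use: "A summed score across these four items will be used as a measure of". The quantity meant is the intervention's reach among staff, and the sentence places that use in the main trial analysis without saying what role the score has there.
- **The PRASE intervention process.** "Control wards will receive no intervention during the study duration".
- **Trial analysis.** The harm-free care model adjusts for the minimisation factors and baseline harm-free care. The PMOS domain models adjust for the minimisation factors and ward-average baseline PMOS. Neither names fidelity or reach.

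**The concern.** A covariate in a treatment-effect model should be fixed before allocation, or at least be unaffected by it. Fidelity is a consequence of allocation. Only intervention wards have anything to adhere to, and adherence is the route by which the intervention is meant to work. Once it is in the model beside the arm indicator, the arm coefficient no longer answers the primary objective, which is whether PRASE improves safety over 12 months.

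The article gives no value for control wards, does not restrict the model to intervention wards and does not label it exploratory. Readers could therefore be shown two arm effects side by side, only one of which is a randomised comparison, with nothing to tell them which to believe. Reach is measured at 12 months and is likely to be related to arm, so it would raise the same difficulty if used as a covariate.

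**Working it through.** **1. The plan's own figure.** Inputs from Estimate of sample size: effect size 0.3, alpha 0.05 (two-sided assumed), power 80%, 25 patients per ward, ICC 0.05.

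- Individually randomised: 2(1.96 + 0.84)²/0.3², rounded up to 175 per arm.
- Design effect: 1 + 24 × 0.05 = 2.2, so 175 × 2.2 = 385 per arm.
- 385/25 = 15.4, rounded up to 16 wards per arm, or 32 in all.

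The stated 32 wards reproduce. Power with 16 wards of 25 per arm is 0.82 by the normal approximation and 0.79 by a t-test on ward means. Nothing below changes this number.

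**2. What the arm coefficient becomes.** Let T be arm, F fidelity (0 in control wards) and b the fitted slope on F. Every control ward has F = 0, so b is estimated from the 16 intervention wards alone. The fitted arm effect is

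(intervention mean − control mean) − b × (mean F in intervention wards).

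This is the contrast for an intervention ward with F = 0. If F is instead left missing for control wards, those 16 wards drop out and T is constant, so no arm effect can be estimated.

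**3. Loss of precision.** Let s be the residual ward-level SD, and m and sd the mean and SD of F in intervention wards.

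- Without F: variance = s²(1/16 + 1/16) = 0.125 s², so SE = 0.354 s.
- With F: variance ≈ s²(0.125 + m²/(13 sd²)). The 13 comes from the expected inverse sum of squares for 16 wards, taking F as roughly normal.

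The article gives neither m nor sd, so a range is shown:

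| Assumed m, sd | m²/(13 sd²) | SE with F | Ratio to 0.354 s |
|---|---|---|---|
| 1.5, 1.0 | 0.173 | 0.546 s | 1.5 |
| 2.0, 0.6 | 0.855 | 0.990 s | 2.8 |
| 2.5, 0.4 | 3.005 | 1.769 s | 5.0 |

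**4. Shift in the estimate, on the plan's scale.** The ward-level SD is √(0.05 + 0.95/25) = √0.088 = 0.297. Simulations of 16 + 16 wards used m = 2, sd = 0.6, scores cut at 0 and 3, control wards at 0, and 5,000 trials per scenario. Arm and F correlate at about 0.93.

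| Assumed truth | Without F: estimate (SE), share significant | With F: estimate (SE), share significant |
|---|---|---|
| Effect 0.30, F unrelated to outcome | 0.30 (0.104), 79% | 0.30 (0.295), 18% |
| Effect 0.30, wholly through F (0.15 per point) | 0.30 (0.106), 77% | 0.005 (0.294), 5% |
| Effect 0.30, better wards adhere more (correlation 0.3) | 0.30 (0.104), 79% | −0.006 (0.288), 5% |
| No effect, better wards adhere more (correlation 0.5) | 0.00 (0.104), 5% | −0.51 (0.277), 44% |

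The second row follows from step 2: 0.30 − 0.15 × 2 = 0. So does the fourth, apart from the cut-off at 0 and 3: the slope is 0.5 × 0.297/0.6 = 0.247, and 0 − 0.247 × 2 = −0.49.

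**5. Reach.** Process evaluation analysis puts the score in the main trial analysis. Trial analysis specifies both primary models without it. The two sections do not agree, and neither gives reach a role.

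**The case against.** The case on the other side is substantial. Use of the fidelity score is permitted, not required, and results without it are anticipated. Both primary models are specified without either score. A full analysis plan is promised before any analysis. The wording on fidelity would also fit a dose-response analysis confined to intervention wards. The figures in step 4 rest on assumed inputs, and in the first scenario the two estimates agree and only precision is lost.

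Most of this stands, and it rules out several stronger readings that a reader might infer:

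- *That the trial's treatment effect loses its meaning.* It does not. The unadjusted estimate is planned and is unbiased in every scenario above. The problem lies only in the adjusted model.
- *That reach is a planned covariate, and zero or undefined in control wards.* The article never calls it a covariate. The questionnaire is headed as going to all staff, and its items include exposure to data collection, which control wards also have.
- *That post-randomisation values of sickness, staffing and discharges will enter the primary model.* The text is "Ward level covariates will be added to the primary model in order to explore their influence". This is exploratory, and no time point is given for the values used.
- *That scoring is open to knowledge of outcomes.* Adherence is said to be "largely based on satisfaction in relation to each of the moderating factors", but three team members first score independently, and the full framework is in an appendix not shown here. The article does not establish the point either way.

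What the objection does not remove is the stated option itself. Presenting results with and without fidelity is no safeguard while the adjusted result carries no label, no rule for control wards and no statement that it is not a treatment effect.

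**Conclusion.** The point holds for any between-arm model that includes fidelity, and for reach if it is used as a covariate. Such a model does not estimate the randomised effect. This follows from the structure of the score and needs no numerical assumption.

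The size does need assumptions. The SE inflation of about 1.5- to 5-fold rests on a fidelity mean of 1.5 to 2.5 and SD of 0.4 to 1.0 in intervention wards, with control wards at 0. The fall to about 0 assumes that benefit acts wholly through fidelity. The false-positive rate of 44% assumes a correlation of 0.5 between ward quality and adherence. None of these values is in the article, so they show direction and rough size only.

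The primary estimate without the scores and the 32 wards are unaffected. This is a correction to a stated secondary use of the scores, together with an inconsistency between two sections over reach.

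**What to change.** 1. Under Assessment of fidelity, replace the covariate option with a statement that all models estimating the effect of allocation exclude fidelity and reach.
2. Reconcile Process evaluation analysis with Trial analysis: remove reach from the main trial analysis, or state there that it is used only descriptively or in exploratory work.
3. Confine both scores to analyses labelled exploratory. The natural one is the association between score and outcome within the 16 intervention wards, reported as non-randomised. Optionally, add a complier-average analysis with allocation as instrument. That requires a definition of adherence fixed in advance and a stated assumption that allocation affects outcome only through adherence.

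The cost is a few sentences in the protocol and analysis plan and one small exploratory analysis. Data collection and sample size do not change.
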